## 2. Materials and Methods

### 2.1. Study Design

This study follows a randomized, controlled experimental design with parallel groups (1:1 allocation ratio), aimed at evaluating and comparing the effects of two types of training protocols on MC in children aged 6 to 10 years. This methodology is used considering the conclusions of the systematic review and the fact that the main researcher is an athletics coach.

The participants will be ecologically assigned into one of two intervention groups, depending upon the training schedule chosen by their parents, according to their availabilities, and being given no prior indication of which of the two programs will function on which schedule: (i) Intervention Group A (IG_A) will receive athletics-based training exclusively, three times per week for 12 consecutive weeks, with each session lasting 60 min; and (ii) Intervention Group B (IG_B) will receive a combined program consisting of athletics-based training twice per week and one additional session per week involving a complementary activity (gymnastics, handball, or motor games), also over 12 weeks and with 60 min sessions.

All the participants will undergo MC assessments at two times: (i) at baseline (T0), prior to the beginning of the intervention; and (ii) at post-intervention (T1), immediately following the 12-week training period.

The post-intervention evaluations will take place three days after the final training session, always in the afternoon, to ensure consistency in the testing conditions. Figure 1 illustrates the participant flow and intervention timeline for the trial.

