## 4. Statistical Analysis

The required sample size was calculated using the G*Power software (3.1.9.4; Heinrich Heine University Düsseldorf, DE). As the aim is to detect differences in the KTK3+ between the two groups, and considering that the analysis will be performed on the outcomes, a between–within ANOVA-RM (2 [groups] × 2 [time points]) will be conducted, anticipating a ‘large’ effect size (f = 0.4) based on similar previous studies using the KTK3+ [26,27,36], with an α = 0.05, a statistical power of (1 − β) = 0.95, correlated dependent variables with an r = 0.50, and a violation of sphericity (ε) = 0.80. This analysis will require a total sample size of 18 individuals per group. Thus, the study should start with an additional 15% of the planned sample size for each group to account for potential dropouts as suggested by several authors (e.g., [37]). It will also be comparable to previous school-based MC studies that employed the KTK3+ as an outcome measure in early childhood and primary education contexts [24,25], considered adequate for the study objectives and the planned statistical analyses. The means and standard deviation will be calculated for all the studied variables. The normality and homoscedasticity will be verified with the Shapiro–Wilk (n < 50) and Levene’s tests, respectively. The statistical analyses will be conducted in IBM SPSS Statistics version 27. The referred to ANOVA-RM will be applied to each of the four KTK3+ battery tests independently and to the KTK3+ battery results as a whole, namely to its raw results and to its Global Motor Quotient. Thus, we will be conducting six distinct analyses and will extract conclusions from each of them, with the latter two being the most important, as global results. Nevertheless, if specificities can be found for the other four, we intend to address and to consider them.

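### The stated inputs do not give 18 per group for any term of the 2 × 2 ANOVA-RM, epsilon of 0.80 cannot occur with two time points, and the powered term and effect-size scale are not stated

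*Protocol article*

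**What the plan says.** Section 4 of the Protocol article describes a G*Power calculation for a between–within ANOVA with two groups and two time points. The aim is put this way: "As the aim is to detect differences in the KTK3+ between the two groups". The effect is given as a large "effect size (f = 0.4) based on similar previous studies using the KTK3"+ battery, with α = 0.05, power 0.95, a correlation of 0.50 and "a violation of sphericity (ε) = 0.80". The result is: "This analysis will require a total sample size of 18 individuals per group". A dropout allowance of 15% is then added on top.

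Section 2.1 (Study Design) fixes the number of measurements: "All the participants will undergo MC assessments at two times", namely baseline and post-intervention. Hypotheses (iii) and (iv) in section 1 (Introduction) concern greater improvement in IG_B than in IG_A. That is the group-by-time term.

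**The concern.** Three things do not fit together.

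- **The number.** A sample size should follow from its inputs. Here 36 children in total does not come out for any term of the model.
- **Epsilon.** With two time points there is one within-subject contrast, so sphericity holds trivially and no violation can be entered.
- **What was sized.** The stated aim, differences between the groups, can be read as the group main effect, while the hypotheses point to group-by-time. G*Power offers more than one scale for f in this test, and the article does not say which was used. The result sentence also calls one figure both a total and a per-group number.

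What is at stake is how the result is read. A published 95% power claim invites the reader to take a non-significant comparison as good evidence that the programmes do not differ. Whether that is fair depends on the size of effect the 95% refers to, and the article leaves this open.

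**Working it through.** **Inputs** (section 4 unless noted): f = 0.4; α = 0.05; target power 0.95; r = 0.50; epsilon 0.80; k = 2 groups; m = 2 measurements (also section 2.1); 1:1 allocation (section 2.1). Stated result: 18 per group, so N = 36.

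**Formulas** (noncentral F, as in G*Power)

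- Group-by-time or time, default scale: λ = f²·N·m·ε/(1 − r); df1 = (m − 1)ε; df2 = (N − k)(m − 1)ε.
- Group main effect: λ = f²·N·m/(1 + (m − 1)r); df 1 and N − 2.
- Group-by-time, SPSS scale: λ = f²·(N − k)(m − 1)ε. Cohen scale: λ = f²·N·(m − 1)ε.

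**Step 1: try to reproduce the plan's figure.** Smallest even N with power of at least 0.95, and power at N = 36:

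| Term and scale | ε | N needed (total) | Power at N = 36 |
|---|---|---|---|
| Group-by-time or time, default | 1 | 24 | 99.7% |
| Group-by-time or time, default | 0.80 (forced) | 28 | 98.9% |
| Group main effect | n/a | 64 | 76.8% |
| Group-by-time, Cohen scale | 1 | 84 | 64.5% |
| Group-by-time, SPSS scale | 1 | 86 | 62.0% |

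Examples at N = 36: for group-by-time with ε = 1, λ = 0.16 × 36 × 2/0.5 = 23.04 on 1 and 34 df, power 0.997. For the group main effect, λ = 0.16 × 36 × 2/1.5 = 7.68 on 1 and 34 df, power 0.768.

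With epsilon forced to 0.80, the Cohen and SPSS scales need 100 and 102. The result closest to 36 is 28, which is 8 children away, so rounding does not explain the gap. A total of 36 appears only if a stated input is changed. For group-by-time, for example, r = 0.2 with ε = 1, or r = 0.3 with ε = 0.80, would give it.

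**Step 2: epsilon.** Its lower bound is 1/(m − 1). With m = 2 this is 1/1 = 1, which is also its upper bound. A value of 0.80 is not possible.

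**Step 3: what f = 0.4 means for group-by-time.** On the default scale the interaction shifts each of the four cell means by ±f SD, so the difference in change is 4f = 4 × 0.4 = 1.6 SD. On the Cohen scale, equating the two λ gives f·√(8(1 − r)) = 0.4 × √4 = 0.8 SD at r = 0.50. The same 0.4 therefore stands for two effects that differ by a factor of two.

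**Step 4: what 18 completers per group can detect** (group-by-time, ε = 1, α = 0.05). Solve λ = f²·36·2/(1 − r) for the required power and multiply f by 4. The article gives r = 0.50; the values 0.3 and 0.7 are assumptions to show the range.

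| r | 80% power | 95% power |
|---|---|---|
| 0.3 | 1.14 SD | 1.46 SD |
| 0.50 | 0.96 SD | 1.24 SD |
| 0.7 | 0.74 SD | 0.96 SD |

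At r = 0.50, for instance, f = 0.240 gives 80% power (4 × 0.240 = 0.96) and f = 0.309 gives 95% (4 × 0.309 = 1.24).

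**The case against.** The strongest reply is that nothing here shows too few children. Hypotheses (iii) and (iv) are tested by group-by-time. On G*Power's default scale that term needs 12 per group, or 14 with epsilon forced to 0.80, and the plan has 18. On that reading the power is 99.7%, above the 95% claimed. Entering epsilon 0.80 also raises N, from 24 to 28, so that error is conservative. All of this stands.

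It limits the point without removing it. The favourable reading has to be supplied by the reader, it still does not return 18 per group, and it holds for an effect of 1.6 SD that the article never states.

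Some stronger readings are tempting but lack support:

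- A reader might infer that the trial is badly underpowered for realistic effects. The article gives no expected difference in change, and its sources for f = 0.4 are not at hand. Any smaller benchmark is the reader's choice and depends on r: at 0.8 SD and N = 36, power is 64.5% with r = 0.50 but 85% with r = 0.7.
- A reader might infer that a software total of 18 was mistaken for a per-group figure. A total of 18 can be produced in more than one way, such as power 0.80 with epsilon 0.80, or four measurements with epsilon 0.80. Each departs from the stated inputs, and the article shows none of them.
- A reader might object to the dropout allowance. Adding 15% gives 18 × 1.15 = 20.7, so 21 starters, and 21 × 0.85 = 17.85 completers. A shortfall of 0.15 of a child is trivial.

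**Conclusion.** The sample-size statement is wrong as written. No standard reading of the stated inputs pairs 95% power with 18 per group, and epsilon of 0.80 is impossible in this design. Power at 36 completers is about 62–65%, 76.8% or 99.7%, depending on the effect-size scale and the term, neither of which is stated.

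It would go too far to say that 95% power is missed on every reading. It is exceeded for group-by-time on the default scale. It is missed if the group main effect was meant, or if f = 0.4 is on the SPSS or Cohen scale.

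The power figures rest on the noncentral-F formulas above, r = 0.50 as stated, 18 completers per group and α = 0.05 for a single test.

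**What to change.** Rewrite the sample-size sentences in section 4 and keep 18 per group:

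- Name group-by-time, the term that tests hypotheses (iii) and (iv), as the sized test.
- Set epsilon to 1 and remove the reference to a violation of sphericity.
- State which G*Power effect-size scale f refers to.
- Give the size as 18 per group, 36 in total, so that total and per-group figures are not mixed.
- Replace the 95% claim at f = 0.4 with: 18 completers per group give 80% power for a difference in change of 0.96 SD and 95% power for 1.24 SD at r = 0.50. Add the range for other correlations (80%: 1.14 SD at r = 0.3 and 0.74 SD at r = 0.7; 95%: 1.46 SD and 0.96 SD).
- If motor-quotient points are also given, label them as assuming an SD of 15 (0.96 × 15 = 14.4 points; 1.24 × 15 = 18.6 points). That SD is only implied by the classification bands in section 2.4.4, and club athletes may differ from the norm population.

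The cost is one rewritten paragraph and a less favourable stated detectable effect. No extra children are needed, and the design and the planned test stay as they are.

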The results of each item are compared with the normative values provided by the authors, and each item is assigned a quotient. The sum of the four quotients represents the global motor quotient (GMQ), which can be presented as a percentage or absolute value, making it possible to classify children for each age and sex according to their level of coordination development. For the total KTK3+ MQ-score, a classification of 5 levels of MC based on the normal distribution can be made [34]: (i) values below 70 are seen as an indicative of “severe gross MC disorder”; (ii) values between 71 and 85 are considered to represent “moderate gross MC disorder”; (iii) values between 86 and 115 are seen as “normal gross MC proficiency”; (iv) values between 116 and 130 are seen as “good gross MC proficiency”; and (v) values above 131 point to “high gross MC proficiency”. Before the initial assessment there will be practitioner training of the research team that will be assessing the KTK3+ to assure high inter-rater reliability.

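### Minor: the group-by-time test assumes equal spread of gains, the named checks may not examine that, and group sizes are not controlled; an unequal-variance comparison of gains costs almost nothing

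*Protocol article*

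**What the plan says.** The protocol article, section 4 (Statistical Analysis), fixes the model: "a between–within ANOVA-RM (2 [groups] × 2 [time points]) will be conducted". The model is applied separately to the four KTK3+ tests, to the raw battery result and to the Global Motor Quotient, which makes six analyses.

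On assumptions it says "The normality and homoscedasticity will be verified with the Shapiro–Wilk (n < 50) and Levene’s tests, respectively". It does not say whether the checks apply to the T0 and T1 scores, to the gains or to residuals, and it does not say what follows a failed check. The sentence just before reads "The means and standard deviation will be calculated for all the studied variables", which suggests the scores but does not settle it.

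On group sizes, section 2.1 states 1:1 allocation, and section 4 says "This analysis will require a total sample size of 18 individuals per group", plus 15% per group. Section 2.1 also places children in groups "depending upon the training schedule chosen by their parents, according to their availabilities". Section 2.2 excludes children below 80% attendance and, in IG_B only, those below 80% of the complementary sessions.

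**The concern.** The superiority hypotheses, (iii) and (iv) in the Introduction, are tested by the group-by-time interaction. With two time points that interaction depends only on each child's gain, and it pools the variance of the gains across the groups. Pooling is harmless when the groups are the same size. When both the sizes and the spreads differ, the standard error is wrong. It is too small if the smaller group has the wider gains, and too large if the larger group does.

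The spread of a gain depends on the T0 SD, the T1 SD and the correlation between them. Two groups can therefore have identical score SDs at both times and still differ in the spread of their gains. A check on the scores could pass while the assumption behind the superiority test fails. At stake is a modest departure from the nominal 5%, in either direction, on any of the six outcomes.

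**Working it through.** **Plan's own figure.** The sample-size inputs are "anticipating a ‘large’ effect size (f = 0.4") and "with an α = 0.05, a statistical power of (1 − β) = 0.95, correlated dependent variables with an r = 0.50", with ε = 0.80. For the interaction, λ = f²·N·m·ε/(1 − r), df1 = (k − 1)(m − 1)ε and df2 = (N − k)(m − 1)ε, with k = m = 2. This needs 28 children in total at ε = 0.80 and 24 at ε = 1. The stated 36 is not reproduced; it exceeds what the interaction needs. That is a separate matter. Only the planned sizes are used here: 18 per group, or 18 × 1.15 = 20.7, about 21 per group at entry.

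**Step 1: what the test assumes.** With two times, F(group × time) = t², where t is the pooled-variance two-sample t on T1 − T0. Hence normality and equal variance are required of the gains.

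**Step 2: scores and gains can disagree.** Var(gain) = s0² + s1² − 2·r·s0·s1. Take s0 = s1 = 1 in both groups.
- r = 0.80: gain SD = √0.40 = 0.632
- r = 0.55: gain SD = √0.90 = 0.949, ratio 1.5
- r = 0.20: gain SD = √1.60 = 1.265, ratio 2.0

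**Step 3: why group size matters.** Take 22 children with gain SD 1 and 14 with gain SD 2.
- True variance of the difference: 1/22 + 4/14 = 0.331
- Expected pooled estimate: [(21 × 1 + 13 × 4)/34] × (1/22 + 1/14) = 2.147 × 0.1169 = 0.251
- The true standard error is √(0.331/0.251) = 1.15 times the one used.

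With the wider gains in the 22 instead, the ratio is √(0.253/0.333) = 0.87. At 18:18 both expressions equal 0.278 and the ratio is 1.

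**Step 4: error of the nominal 5% test.** Normal gains, no true effect, 200,000 simulated trials per setting. The document gives neither the gain SDs nor the realised sizes; the ratios and splits are assumptions.

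| Sizes | Wider gains in smaller group, ratio 1.5 / 2 | Wider gains in larger group, ratio 1.5 / 2 |
|---|---|---|
| 18:18 or 21:21 | 5.0–5.3% | same |
| 20:16 | 6.1% / 6.9% | about 4% / about 4% |
| 22:14 | 7.2% / 9.0% | 3.4% / 2.7% |
| 24:12 | 8.6% / 11.5% | 2.7% / 1.8% |

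Welch's t on the gains ran at 4.9–5.2% throughout.

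**Step 5: what Levene would see** (4,000 trials per setting).
- Equal score SDs with different pre-post correlation, as in step 2: Levene on T0 and on T1 each rejects in about 5% of trials, its chance rate.
- Wider T1 spread in one group (SD 1.5 against 1): Levene at T1 rejects in about 30%.
- Levene on the gains, ratio 1.5: rejects in about 30%. Among trials that pass it at 22:14, the pooled test still runs at about 8%.

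**Step 6: can sizes become unequal?** Table 2 has 12 complementary sessions, so 80% is 9.6, meaning at least 10. An IG_B child who misses three Thursdays and nothing else attends 33 of 36 sessions (92%) but 9 of 12 complementary ones (75%), and is excluded. An IG_A child with the same record stays. Slot choice by parents adds imbalance that nothing in the plan limits.

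**The case against.** The strongest reply is that the planned design is 1:1, where the test holds its level, so nothing goes wrong unless three unstated things coincide: clearly unequal sizes, clearly unequal gain spreads and the wider spread in the smaller group. That stands. Nothing in the article suggests a 2:1 split, and section 2.5.1 says the complementary session falls on a day with normally higher attendance, which weakens the case that IG_B will shrink much.

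Four stronger readings are tempting, and the document does not support them.
- *The checks are run on the scores.* The text never says so; this is inferred from the neighbouring sentence.
- *The checks decide which analysis is used, and 24 Shapiro–Wilk tests (6 outcomes × 2 groups × 2 times) would raise a false alarm with chance 1 − 0.95²⁴ = 71%.* No decision rule or fallback is stated, testing in every cell is assumed, and the 71% needs independence among outcomes that overlap and are measured twice on the same child.
- *Unequal spread always goes unseen.* Step 5 shows that when it comes from the T1 spread, Levene at T1 finds it about as often as Levene on gains would.
- *Normality checks would mainly reflect the age mix.* That could apply to raw scores, but section 2.4.4 describes the quotient as "making it possible to classify children for each age and sex according to their level of coordination development", so it does not carry over to the Global Motor Quotient.

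It is also fair that the quantity checked is a detail an article may leave to the analysis plan. What remains is that the article does fix the pooled-variance test, and a better-behaved comparison is available at almost no cost.

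**Conclusion.** The point holds as a minor one. The planned interaction test assumes equal spread of gains; the named checks may not examine that, and at this sample size would often miss it even if they did. At the planned equal sizes there is no practical problem. If sizes drift apart and gain SDs differ 1.5 to 2 fold, the 5% test runs at roughly 6–11% over splits from 20:16 to 24:12 when the smaller group has the wider gains, and at roughly 2–4% when the larger group does. These ranges rest on assumed splits and spreads and on normal gains. They show what is possible and do not predict this trial's error rate.

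**What to change.** State in advance that, for each of the six outcomes, the IG_B minus IG_A difference in gain (T1 − T0) is tested and given a confidence interval with unequal variances (Welch/Satterthwaite), whatever Levene or Shapiro–Wilk show. If a baseline-adjusted model is preferred, use HC3 standard errors (not simulated here). Look at residuals of the gains descriptively only, not to choose the test. Adding a Levene test on the gains is not a substitute, as step 5 shows.

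The cost is a sentence in the analysis plan. With equal spreads and a true difference of one gain SD (assumed), power is 82.9% with Welch against 83.0% pooled at 18:18, and 76.9% against 78.5% at 24:12, a loss of 1.6 points.

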Middle childhood, between the ages of 6 and 10, is a critical period for motor skill acquisition, characterized by rapid neuromuscular maturation, growth in physical capacities, and heightened adaptability to training stimuli. The evidence from school- and community-based interventions shows that structured PA (e.g., games, plyometric training, dance, and sports) or aquatics (e.g., swimming) consistently improves FMSs, coordination, and overall MC in this age group [16,17,18]. Aquatic programs have demonstrated significant gains in both global and specific motor skills, even over short durations, while land-based interventions have been shown to enhance complementary domains, such as strength, agility, and locomotor proficiency [19,20]. Collectively, the literature highlights that providing diverse, developmentally appropriate movement experiences during this sensitive growth window not only optimizes motor development but also supports long-term physical literacy and active lifestyle habits.

In this context, it becomes essential to assess the effects of systematic and structured training programs targeting MC development in early school-age children. Standardized tools, such as the Körperkoordinationstest für Kinder (KTK) [21], Test of Gross Motor Development of Ulrich [22], and Motor Assessment Batteries for Children (MABC) of Henderson and Sugden [23], have been widely used to evaluate MC due to their reliability and suitability for children aged 6 to 10 years.

Thus, the aim of this study is to design and evaluate a 12-week athletics-based training program for children aged 6 to 10, assessing its effects on MC. The hypotheses are as follows: (i) There will be significant improvement in MC after the 12-week intervention. (ii) There will be significant between-group differences in MC levels post-intervention. (iii) There will be significant improvement in MC of IG_B group after the 12-week intervention compared to the IG_A. (iv) The multi-activity program will lead to greater MC improvement in the IG_B group.

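### The covariate-free 2 × 2 ANOVA-RM uses the baseline score inefficiently, and its group main effect does not test hypothesis (ii); ANCOVA on T1 is a cheap improvement

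*Protocol article*

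**What the plan says.** Section 4 states the purpose and the model: "As the aim is to detect differences in the KTK3+ between the two groups", and "a between–within ANOVA-RM (2 [groups] × 2 [time points]) will be conducted". No covariate is named. The same model serves six analyses: the four single tests ("The referred to ANOVA-RM will be applied to each of the four KTK3+ battery tests independently"), the raw battery result and the Global Motor Quotient (GMQ). The last two are ranked as most important.

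The planning inputs are "effect size (f = 0.4) based on similar previous studies using the KTK3"+ battery, "with an α = 0.05, a statistical power of (1 − β) = 0.95", "correlated dependent variables with an r = 0.50" and "a violation of sphericity (ε) = 0.80", giving 18 children per group.

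The Introduction lists four hypotheses. The second is "There will be significant between-group differences in MC levels post-intervention", a statement about T1. The third and fourth concern greater improvement in IG_B than in IG_A. Section 4 does not say which term of the ANOVA (group, time or group-by-time) answers which hypothesis.

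Two further passages bear on the point. The section on KTK3+ test application refers item results to norms and uses the GMQ to classify children by age and sex. Section 2.1 (Study Design) lets group follow the training schedule that parents choose, without their knowing which program runs in which slot. Sections 2.2 and 2.4.1 call the allocation random.

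**The concern.** Every child has a T0 score, and in a trial of 36 that score is the main source of extra precision. A 2 × 2 ANOVA-RM uses it only by subtraction, which in effect fixes the slope of T1 on T0 at 1. At the plan's correlation of 0.50 and equal SDs, the slope is 0.50, so subtracting the whole baseline adds noise.

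The second issue is the match between hypothesis and term. Hypothesis (ii) is about the groups at T1. The group-by-time term is about differences in change. The group main effect is about the average of T0 and T1, and half of that average was measured before any training. An analyst who looks for a between-group result in the SPSS output for this model will find the group main effect, and it is the wrong quantity for (ii).

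At stake are precision that costs nothing to recover and a clear answer to one of the four hypotheses.

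**Working it through.** **Plan's own figure.** I used the G*Power repeated-measures formulas with f = 0.4, α = 0.05, power 0.95, r = 0.50, two groups and two times.
- Interaction: λ = f²·N·2·ε/(1 − r). This needs 24 children in total at ε = 1, or 28 at ε = 0.80.
- Between-group term: λ = f²·N·2/(1 + r). This needs 64 in total.
- The stated 36 (18 per group) comes out of neither. With two time points ε is necessarily 1, so 0.80 cannot apply.

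This is a separate matter. Below I take 18 per group as given.

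**Variance of each estimator.** Assume equal SDs at T0 and T1 and comparable baselines. The unit is σ²(1/n₁ + 1/n₂).
- Change score (group-by-time): 2(1 − r) = 2 × 0.50 = 1.00
- T1 alone: 1.00
- ANCOVA of T1 on group and T0: 1 − r² = 1 − 0.25 = 0.75
- Group main effect: variance (1 + r)/2 = 0.75, but for half the T1 difference. Rescaled to the full difference it is 4 × 0.75 = 3.00, four times the ANCOVA variance.

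The ratio of ANCOVA to change score is (1 − r²)/[2(1 − r)] = (1 + r)/2 = 0.75, a 25% cut.

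**Cost of estimating the slopes at N = 36.** With p covariates the ANCOVA variance is multiplied by (N − 3)/(N − 3 − p).
- T0 only: 33/32, so 0.75 × 1.031 = 0.773, a cut of about 23%. Simulated ratios were 0.76 to 0.78.
- T0, age and sex, the last two assumed to predict nothing beyond T0: 33/30, so 0.75 × 1.10 = 0.825, a cut of about 18%. Simulated ratios were 0.81 to 0.82.

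**Sensitivity to r** (ratio of ANCOVA variance to change-score variance)

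| r | Large sample, T0 | N = 36, T0 | N = 36, T0 + age + sex |
|---|---|---|---|
| 0.3 | 0.65 | 0.67 | 0.72 |
| 0.5 | 0.75 | 0.77 | 0.83 |
| 0.7 | 0.85 | 0.88 | 0.94 |
| 0.8 | 0.90 | 0.93 | 0.99 |
| 0.9 | 0.95 | 0.98 | 1.05 |

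The article gives no observed T0–T1 correlation for the KTK3+; 0.50 is a planning input.

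**Power at 18 per group, r = 0.50, for an assumed T1 difference of 0.8 SD with equal baselines.** The 0.8 SD is an assumption: it is f = 0.4 read as an ordinary two-group effect, d = 2f.
- Change score: standard error √(2/18) = 0.333, power 64.5%
- ANCOVA with T0: about 75–76% in simulation
- ANCOVA with T0, age and sex: about 72–73%
- Group main effect (estimating 0.4 SD): 27%

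For an assumed 1.0 SD, simulated power is 83% (change score), 91% (ANCOVA with T0) and 39% (group main effect).

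**The case against.** **The plan never says it will use the group main effect.** This is correct. A reader might infer that hypothesis (ii) will be judged on that term, but section 4 names only the model. A simple contrast at T1 could sit in a fuller analysis plan. So the 27% describes a test the plan does not commit to. What stands is that neither standard between-group term of the stated model estimates (ii). A plain T1 contrast would, but at variance 1.00 against 0.75.

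**The interaction is a proper test.** This also stands. Group-by-time validly addresses (iii) and (iv), the superiority question stressed in the Discussion. The fault there is inefficiency only.

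**Age and sex are partly dealt with.** A reader might infer that any age or sex imbalance passes straight into the raw-score comparison. It does not: a stable difference in level cancels in a change score, and only gains that depend on age or sex could confound it. The GMQ is already referred to norms. Section 4 also does not say whether the four single tests are analysed as raw scores or quotients, so only the raw battery result is certainly unnormed.

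**A power of 64.5% is not the trial's power.** The 0.8 SD is assumed. Read as G*Power's interaction effect, f = 0.4 gives λ = 0.16 × 36 × 2/0.5 = 23.04, a difference in change of √23.04 × 0.333 = 1.6 SD, and power of 0.997 (0.989 with ε = 0.80).

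**ANCOVA's advantage needs comparable baselines.** This is the strongest objection. Suppose a T0 gap of 0.5 SD, r = 0.50 and identical gains in both groups. The change score gives 0, while ANCOVA gives 0.5 × (1 − 0.5) = 0.25 SD. Which is right depends on how families sorted themselves, and the data cannot settle that. Parents' ignorance of which program runs in which slot makes selection on the program less likely, but schedule choice can still track age or family circumstances. This is a reason to report both estimates, not to omit ANCOVA.

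**Conclusion.** The point holds as a cheap improvement. The stated model gives up about 23–25% of variance at 18 per group relative to ANCOVA with T0. The saving is about 18% if age and sex are added and predict nothing more; they could recover precision if they do predict T1 beyond T0. These figures assume r = 0.50, equal SDs at T0 and T1, and comparable baselines. In large samples the saving falls to 10% at r = 0.8 and 5% at r = 0.9. At N = 36 with age and sex added it is about nil at 0.8 and turns into a small loss at 0.9.

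The group main effect estimates half the T1 difference when baselines are equal and should not be read as the answer to (ii). The documents do not support the stronger statements that the plan has chosen that term, that its test of (iii) and (iv) is wrong, or that all six outcomes are left unadjusted for age and sex.

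**What to change.** 1. For each outcome, regress T1 on group and T0. Add age and sex for raw scores; leave them out for the normed GMQ. State for the four single tests whether raw scores or quotients are analysed.
2. Report the adjusted T1 difference with its 95% CI as the answer to hypothesis (ii).
3. Report the group-by-time (change-score) estimate with its 95% CI alongside, for (iii) and (iv).
4. State that the ANOVA-RM group main effect is not used.
5. State that, because allocation follows parental choice of schedule, the two estimates can diverge if baselines differ, and that neither removes selection bias.

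The cost is analysis wording only: no new data are needed, and SPSS 27 fits the model. The downsides are one to three extra parameters in a sample of 36, an assumed linear relation with T0, and reliance on comparable baselines.

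### Conclusions are promised from six analyses with no single deciding outcome; for assumed task correlations of 0 to 0.9, the chance of a false group-by-time result is about 21% down to 9.5%

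*Protocol article*

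**What the plan says.** The statistical section sets one 2 × 2 mixed ANOVA (group by time). The only significance level in the article stands among the sample-size inputs: "with an α = 0.05, a statistical power of (1 − β) = 0.95". That ANOVA is to be run separately on each of the four KTK3+ tasks, on the battery's raw results and on the GMQ. The rule for reading the results follows: "we will be conducting six distinct analyses and will extract conclusions from each of them, with the latter two being the most important". On the four tasks it adds: "Nevertheless, if specificities can be found for the other four, we intend to address and to consider them".

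The hypotheses in the Introduction are worded for motor competence in general. Hypothesis (iii) reads: "There will be significant improvement in MC of IG_B group after the 12-week intervention compared to the IG_A". Hypothesis (iv) likewise expects the larger gain in IG_B. Neither names the outcome that settles it. The article states no testing order, alpha split or adjustment.

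**The concern.** The protocol does more than stay silent on multiplicity. It states a rule: conclusions come from all six analyses, two of them lead jointly, and the remaining four are taken up if something shows. Under that rule the false-positive risk attached to any one conclusion is 0.05, but the risk that the report contains at least one false conclusion is larger.

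Two leading outcomes with no order between them also leave it open which result counts if they differ. This has consequences, because the Discussion (Contributions and Future Directions) says that confirmed superiority of IG_B would support recommendations for policy and curricula and lead to efforts to have athletics clubs adopt the activities.

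**Working it through.** **Inputs from the article.** Alpha 0.05; six outcomes; 18 children per group; GMQ formed as the sum of the four task quotients (section 2.4.4).

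**Inputs assumed.** The correlation ρ between task change scores is not given, so it is varied from 0 to 0.9. The construction of the raw total and the task SDs are not given either, so two models are used:
- Model 1: equal task SDs, with raw total and GMQ coinciding.
- Model 2: task SDs in the ratio 1 : 1 : 0.5 : 0.8 for the raw sum, and a GMQ-type standardised sum with added noise, so that the two totals correlate at 0.93 to 0.96.

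**The plan's own figures.** The article states no error rate for the set of six, so there is none to reproduce. Its one computed figure, 18 per group, does not reproduce from the stated inputs. For the interaction, λ = f²·N·m·ε/(1 − r), which at N = 36 is 0.16 × 36 × 2 × 0.8/0.5 = 18.4 and gives power 0.989. A power of 0.95 needs 28 in total (24 with ε = 1). That is a separate matter; 18 per group is taken here as planned.

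**Step 1: independent tests.** 1 − 0.95⁶ = 0.265 for six tests and 1 − 0.95² = 0.0975 for two. These are ceilings, because the totals are built from the tasks.

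**Step 2: dependent tests.** With two time points, the group-by-time test is equivalent to a two-sample t test on change scores. The simulation used 40,000 runs per setting with no true effect. The chance of at least one p < 0.05 is shown as the range over the two models:

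| ρ | All six | Four tasks only | Two global outcomes only |
|---|---|---|---|
| 0 | 0.206–0.215 | 0.185–0.188 | 0.049–0.069 |
| 0.3 | 0.181–0.192 | 0.173–0.178 | 0.051–0.067 |
| 0.5 | 0.162–0.166 | 0.157–0.158 | 0.051–0.065 |
| 0.7 | 0.135–0.136 | 0.130–0.134 | 0.051–0.064 |
| 0.9 | 0.093–0.099 | 0.093–0.094 | 0.049–0.063 |

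Relative to 0.05, the six-test column runs from 0.215/0.05 = 4.3 down to 0.093/0.05 = 1.9. For ρ up to 0.5 it is about 16 to 21%.

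**Step 3: where the inflation arises.** The four tasks alone give nearly the whole six-test rate. The two global outcomes alone add little, since they are almost the same measure. Very unequal task spreads raised their rate to at most 0.078, hence about 5 to 8%.

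**Step 4: how often the two leaders disagree.** If each has size 0.05 and at least one is significant in 0.067 of runs, exactly one is significant in 2 × (0.067 − 0.05) = 0.034. Conflict is uncommon under the null in these models, but no rule resolves it.

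Only one term per ANOVA is counted. Reading the group and time terms as well would raise the rate; that is not sized here.

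**The case against.** The strongest reply is that the article does rank its outcomes. The raw results and the GMQ come first, as global results, the tasks are secondary detail, and hypotheses (i) to (iv) concern motor competence as a whole. Read that way, (iii) and (iv) rest on two nearly identical measures and the error rate is about 5 to 8%. This largely stands for those two hypotheses. It does not remove the commitment to draw conclusions from every analysis, and it leaves the choice between the two leaders open.

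A second reply is that 0.05 appears only in the sample-size sentence, so no threshold per test is actually written, and adjustment details are commonly left to an analysis plan that is not shown. That is fair, and the absence of an adjustment is not itself the point. The point is the stated rule, which an analysis plan would have to change rather than complete.

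A third reply is that the Discussion calls the work a pilot and ties its recommendations to superiority of the programme, not to one task. That is also fair, and it limits how far the consequences can be pressed.

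**Conclusion.** The point holds in a conditional form. With no true effect and 18 per group, the six planned group-by-time tests carry a chance of about 21% (ρ = 0) down to 9.5% (ρ = 0.9) of at least one false result, with 26.5% the ceiling for independent tests. The range rests on the assumed ρ, on 0.05 being used for each test, and on the two models for the totals.

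Three stronger readings go beyond the document:
- A reader might infer a flat three- to fourfold inflation. The multiplier depends on a correlation that the article never gives; at 0.9 it is about two.
- A reader might infer that any single task below 0.05 would be declared confirmation of (iii) or (iv). The article says that conclusions will be drawn from each analysis, not that one task settles superiority in motor competence. The deciding outcome is simply not named.
- A reader might infer that the raw total is dominated by the tasks with the largest spread, or distorted by age. The article neither defines that total nor gives task SDs. In a within-child comparison over 12 weeks, stable age differences in level cancel, so only age-dependent growth could matter.

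**What to change.** Before analysis, add two sentences to 4. Statistical Analysis:
- The group-by-time effect (or the baseline-adjusted group effect) on one global outcome is the single primary test of hypotheses (iii) and (iv), at two-sided 0.05. The GMQ is the natural choice, because section 2.4.4 describes it as built from normative values and able to classify children by age and sex. Any one global outcome fixed in advance would remove the ambiguity.
- The other global outcome and the four tasks are secondary with Holm-adjusted p-values, or exploratory with confidence intervals and not used to confirm (iii) or (iv). If overall control at 0.05 is wanted, the secondary outcomes are tested only after the primary is significant.

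All six analyses remain, data collection is unchanged, and one primary test at 0.05 needs no more children. By comparison, Bonferroni over all six (0.05/6 = 0.00833) would give power at 36 children of 0.932 (ε = 0.8) or 0.972 (ε = 1) on the article's own inputs. The cost is that an isolated significant task can no longer stand as confirmation.
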